**Secondary endpoints:**

Improvement of organ function as evaluated per SOFA score

Changes in laboratory inflammation markers

ICU length of stay

Number of days on mechanical ventilation

**Randomization** Eligible consented patients will be randomized after their stratification by ICU center and two PaO2/FIO2 ratio categories (> 150 and ≤ 150). Randomization will occur in variable block sizes of 4 to 8 patients. We will utilize a web-based randomization service, [randomize.net](http://randomize.net/) to allocate patients to their respective strata prior to the intervention or control therapy. Given the nature of the TPE technology, the intervention will be unblinded (open label); hence, no enrollment concealment will be expedited. However, the lack of allocation concealment will be mitigated as much as possible by the following measures. First, the primary outcome of mortality will not be disputable. Second, we have standardized co-interventions that impact on mortality as much as possible. These interventions include a) concomitant drug therapies for COVID-19, b) algorithms for mechanical ventilation including the early use of prone-ventilation, low tidal volume ventilation and neuromuscular blockade, c) the standard use of a broad spectrum antibiotic(s) for a minimum of 7 days to treat any potential superinfection be a bacterial pneumonia and d) standard criteria to initiate intermittent hemodialysis or CRRT such as hyperkalemia, profound metabolic acidosis, oliguria unresponsive to furosemide challenges of 1-1.5 mg/kg, e) the presence or development of coagulopathy defined as INR > 3.0 or Fibrinogen < 1.0 will be treated in a standard fashion in both the intervention and control group. We will define the date/time of appropriateness for ICU transfer irrespective of treatment allocation and recognizing that some COVID-19 patients randomized to the intervention group may improve to the point of appropriateness to transfer to the medical ward but requiring ICU care only to deliver remaining TPE doses as outlined in the protocol.

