**Statistical analysis**

Continuous data will be summarized as mean ± standard deviation, and compared among groups with student t test or Wilxocon’s rank sum test as appropriate. Discrete data will be summarized as number (%) and compared by chi square or Fisher’s exact test as appropriate. All statistical tests are two tailed, considered significant with p value < 0.05 Survival analysis will be visually presented by Kaplan Meier’s Curve, and compared by hazard ratio. Statistical software SPSS 24.0 will be used.

Crude 30 and 90-days survival distributions between treatment [TPE] and control [no TPE] groups will be described using proportions and Kaplan Meier distributions. Crude differences will be tested using Chi Square test [for proportions] and a log-rank test [for the Kaplan Meier survival distributions]. A multivariable analysis of the primary 30 and 90-days survival outcome will be conducted using a Cox Proportional Hazard model where the main effect of treatment [TPE versus no TPE] and relevant confounding variables: age, gender, admission PaO2/FIO2 ratio, admission APACHE II and SOFA scores, presence of acquired coagulopathy and high vs low CRS group (already defined in previous paragraphs) will be entered into the model a-priori.

Similarly, a logistic regression multivariable model including the aforementioned variables will be fit to determine the independent effect of the TPE treatment on the binary outcome of 30 and 90 days survival.

Daily whole blood and effluent plasma samples will be obtained and assayed for various inflammatory markers IL-6, C-RP, ferritin etc. General estimating equations using random effects models will be used to describe the temporal changes in whole blood [in both treatment and control groups] and effluent plasma [in TPE group only]. Standard comparisons of the change in inflammatory markers using robust variance estimators will be used to compare the changes in these markers between treatment and control group.

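### Randomisation is stratified by ICU centre and P/F category, but the crude tests use neither and the adjusted models omit centre; the tests are conservative if the strata are prognostic.

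*Protocol*

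**What the plan says.** In the Randomization paragraph of the Protocol, patients are "randomized after their stratification by ICU center and two PaO2/FIO2 ratio categories (> 150 and ≤ 150"). Blocking is stated too: "Randomization will occur in variable block sizes of 4 to 8 patients".

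The Statistical analysis section then makes three choices.

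- **Tests.** "Crude differences will be tested using Chi Square test [for proportions] and a log-rank test [for the Kaplan Meier survival distributions"]. No stratification is named. The level is fixed: "All statistical tests are two tailed, considered significant with p value < 0.05".
- **Cox model.** Treatment plus "age, gender, admission PaO2/FIO2 ratio, admission APACHE II and SOFA scores, presence of acquired coagulopathy and high vs low CRS group". These "will be entered into the model a-priori".
- **Logistic model.** "a logistic regression multivariable model including the aforementioned variables will be fit", so it carries the same list.

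Centre appears in no test and no model. P/F appears in both models, as the admission ratio and not the category used for allocation. The word admission is attached to P/F, APACHE II and SOFA; coagulopathy and CRS group have no time point.

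**The concern.** Stratified blocks make the arms more alike on centre and P/F category than simple randomisation would. An unstratified test still counts the between-strata differences in mortality as chance variation between arms. If the strata predict death, its standard error is too large, its true type I error is below 5%, and power is lost. Leaving centre out of the adjusted models has the same effect for the part of the mortality difference that is due to centre.

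This is a choice made in the text, not detail left open: the tests are named and the covariate list is fixed in advance. A later analysis plan that followed the protocol would omit centre.

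A smaller matter is timing. If coagulopathy or CRS group were taken after randomisation, treatment could influence them, and adjusting for them could bias the treatment effect.

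**Working it through.** **Inputs from the Protocol.** About 60 per group and 50% mortality (Study design); at least 20 per arm per centre, so at most 60/20 = 3 centres if that minimum is met; two P/F categories; two-sided 0.05.

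**Assumptions, not in the Protocol.** Three equal centres, half the patients in each P/F category, hence six strata of 10 per arm; mortality by centre and P/F as shown in the table.

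**No figure to reproduce.** The protocol states no power. For context, 50% versus 30% with 60 per arm:
- null SE = √(2 × 0.4 × 0.6/60) = 0.0894
- alternative SE = √((0.25 + 0.21)/60) = 0.0876
- power = Φ((0.20 − 1.96 × 0.0894)/0.0876) = Φ(0.28), about 61%

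**Step 1: why the crude test is conservative.** The chi-square test uses variance p̄(1 − p̄) × 2/60. With arms balanced within strata, the true null variance is the mean of p_s(1 − p_s) over strata, × 2/60. Let r be the ratio of true to assumed variance; the approximate true size is 2Φ(−1.96/√r).

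- Centres 40/50/60%, P/F ±10: strata at 30, 50, 40, 60, 50, 70%. Mean p(1 − p) = (0.21 + 0.25 + 0.24 + 0.24 + 0.25 + 0.21)/6 = 0.2333; r = 0.2333/0.25 = 0.933; size about 4.2%.
- Centres 30/50/70%, P/F ±15: strata at 15, 45, 35, 65, 55, 85%. Mean p(1 − p) = 1.205/6 = 0.2008; r = 0.803; size about 2.9% by this approximation.

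**Step 2: simulation.** 100,000 trials per row, uncorrected tests, control mortality as listed, 20 points lower on TPE. Monte Carlo SE is about 0.15 points for power and 0.07 for type I error.

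| Centres (%) | P/F shift | Type I, chi-square | Type I, CMH | Power, chi-square | Power, CMH | Gain |
|---|---|---|---|---|---|---|
| 50/50/50 | 0 | 5.5 | 5.5 | 61.8 | 61.7 | 0 |
| 40/50/60 | 0 | 5.2 | 5.3 | 62.1 | 62.6 | 0.5 |
| 40/50/60 | ±10 | 4.6 | 4.8 | 62.1 | 64.2 | 2.1 |
| 30/50/70 | ±10 | 3.7 | 4.9 | 62.2 | 68.8 | 6.6 |
| 30/50/70 | ±15 | 3.3 | 5.1 | 58.7 | 67.1 | 8.4 |

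The last two rows are near the limit of what is possible. A 20-point cut takes the lowest stratum to zero; in the final row it is floored there, so the average effect is 19.2 points. Placing the same effect at 60% versus 40% gives gains of 0.9, 4.6 and 7.3 points in the last three rows.

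**Step 3: omitting centre from the logistic model.** 4,000 trials per row, treatment odds ratio 0.375, P/F in both models, no other covariates.

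| Centres (%) | P/F log OR | Power without / with centre | Type I without / with centre |
|---|---|---|---|
| 40/50/60 | 0.85 | 70.6 / 71.7 | 5.1 / 5.4 |
| 30/50/70 | 0.85 | 65.8 / 70.8 | 4.0 / 5.5 |
| 30/50/70 | 1.7 | 60.7 / 64.8 | 4.5 / 5.6 |

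The cost is about 1 point at 40/50/60% and 4 to 5 points at 30/50/70%. If neither factor is prognostic it is negligible (73.9% versus 74.4%). No Cox model or log-rank test was simulated; the same direction is expected there.

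**Step 4: timing of covariates.** The one numerical definition of coagulopathy, "the presence or development of coagulopathy defined as INR > 3.0 or Fibrinogen < 1.0", stands in the Randomization paragraph among the co-treatments standardised in both arms. It does not define the model covariate. The covariate is therefore undated, and so is CRS group.

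**The case against.** The best case for leaving the plan alone is that this is a pilot meant to inform a later trial. It claims no power, and a conservative loss of a few points breaks no stated aim. The tests are openly labelled crude. The 30/50/70% spread appears nowhere in the protocol. Age, APACHE II and SOFA, which Step 3 leaves out, would absorb any part of a centre difference that is due to case mix. Most of this stands. It limits the size of the point but does not explain why the design factors are missing from the tests and centre from a list fixed in advance.

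Four stronger readings do not hold.

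- A reader might infer that the tests are invalid or produce false positives. The error runs the other way.
- A reader might infer that P/F is ignored throughout. Both adjusted models include its admission value.
- A reader might infer that adding centre must narrow the intervals for the hazard and odds ratios. Those measures are non-collapsible and their standard errors need not shrink; the gain is in power and correct size.
- A reader might infer that the plan adjusts for coagulopathy arising on treatment. The Statistical analysis section refers to its presence, among confounders. The wording that covers later development describes co-treatment. This is an ambiguity, not a stated post-randomisation adjustment.

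**Conclusion.** The point holds as a modest, free improvement. The analysis does not follow the randomisation: the crude tests use neither stratification factor and the adjusted models omit centre. The consequence is conservative. Under the assumptions above, the crude test loses about 0 points of power if the strata are not prognostic, about 2 points at 40/50/60% with P/F ±10, and about 6 to 9 points at 30/50/70% with P/F ±10 to 15. Its type I error falls from about 5% to as low as about 3.3%. Mortality by centre is not given, so no single figure in that range can be called the loss in this trial; a wider spread would cost more. The undated coagulopathy and CRS-group covariates are a secondary point of clarification.

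**What to change.** 1. Make the treatment comparison of mortality a Mantel-Haenszel (CMH) test with a Mantel-Haenszel risk difference, and a log-rank test, both stratified by centre and by the P/F category used at randomisation. Keep the crude chi-square and log-rank results as descriptive.
2. Add centre to the Cox model as strata and to the logistic model as a fixed effect. The number of centres depends on further IRB approvals; if many small ones join, use a random effect or pool them.
3. State that the coagulopathy and CRS-group covariates are those present at or before randomisation.

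**Cost.** A change of wording. Centre and P/F category are known at randomisation, and coagulation and inflammatory markers are already collected. With three centres there are six strata of about 20 patients, which is workable. The logistic model gains two parameters: treatment plus seven covariates is 8, rising to 10. At 50% mortality, 0.5 × 120 = 60 deaths are expected, so deaths per parameter fall from 60/8 = 7.5 to 60/10 = 6. Stratifying the Cox model by centre adds no coefficient.

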**Data collection**

Clinical information of all enrolled cases will be retrieved from the hospital electronic/paper records system, including the: baseline demographic data, days of illness duration, presenting symptoms, radiological findings (CXR and Chest CT scans when possible), Sequential Organ Function Assessment (SOFA) and APACHE II scores. Data will be collected upon hospital/ICU admission, and prior to the first TPE session (Day 0) then on days 3, 7, 14, 30 accordingly and/or upon ICU/hospital discharge. Laboratory infectious marker testing results like culture from respiratory, urinary or blood culture will be collected accordingly.

Common laboratory and inflammatory markers (see below) will be collected on a daily basis:

1. CBC differential to include percent and absolute lymphocyte count and percent and absolute neutrophil count

2. Chemistry panel to include Total protein, Albumin, Lactate Dehydrogenase (LDH), Aminotransferases (ALT, AST), Procalcitonin

3. Cardiac biomarkers (e.g. cardiac troponins)

4. CK

5. Ferritin, LDH

6. Full coagulation profile to include PT, APTT, fibrinogen and D-dimer levels

7. C Reactive Protein (CRP) and erythrocyte sedimentation rate (ESR)

8. Interleukin-6

RT-PCR test for SARS-CoV-2 will be done and will be monitored during treatment and at day 14 of recovery or discharge, whatever is later. Also, we will be monitoring: mechanical ventilation (MV) and modes, intranasal oxygen inhalation, non-invasive mechanical ventilation, number of days of MV or nasal oxygen support, medication regimens (i.e., hydroxychloroquine, anti-viral therapies, steroids, tocilizumab, etc.), complications (including acute renal failure, acute coronary syndrome, myocarditis, acute respiratory distress syndrome, GI complications, CNS complications and nosocomial infections).

**Response assessment**

Daily clinical assessment by physician:

Vital signs including temperature, blood pressure, respiratory rate, heart rate. Oxygen saturation, arterial blood gases, and P/F ratios.

Ventilator requirement and the modes employed. Vasopressors requirement, serum lactate levels.

Complete blood counts, liver function tests, urea, creatinine, inflammation markers and electrolytes daily. Glasgow coma scale.

Fluid balance.

X-ray / CT changes.

Organs functions assessment by SOFA score.

TPE doses and frequency requirement.

SARS-CoV-2 RNA will be tested on recovery (or deterioration to determine alternative etiology).

**Monitoring and Safety**

Periodic monthly report will be generated for IRB monitoring. TPE is a routine practice in health care facilities. All known adverse events (AE) and serious adverse events (SAE) will be collected as per the SFDA, CBAHI and AABB reporting standard. SAE will be reported by the study team to the IRB chairman and PI within 12 hours of the event.

**Expected Outcome**

TPE is a cheap modality and readily available. It is expected to save lives and improve the clinical, laboratory and radiological features of at least 60% of the patients severely affected by COVID-19.

**Outcome Utilization**

Decrease in morbidity and mortality of severe COVID-19 disease cost-effectively, leading to improved quality of healthcare in Saudi Arabia.

| --- |
